## 7. Trial treatments

### 7.1 Description of investigational product(s)

Oxygen 100%, medical grade (Conoxia cryogen)

Placebo Air, compressed air medical grade

### 7.2 Dose and administration

Hyperbaric oxygen 240 kPa for 90 minutes (with 10 min compression time, two air breaks and 10 minutes decompression time). The number and frequency of treatments and timing will depend on the subject's tolerance and available resources at the discretion of the attending physician, but the recommended interval is 2–5 treatments per week with a maximum of 10 treatments within 6 weeks from randomization. To satisfy the treatment compliance, a subject need to complete at least 5 treatments.

Placebo (134 kPa Air, with 5 min compression time, and 5 min decompression to 120 kPa, two air breaks will be reported to the subjects). The number and frequency of treatments and timing will depend on the subject's tolerance and available resources at the discretion of the attending physician, but the recommended interval is 2–5 treatments per week with a maximum of 10 treatments within 6 weeks from randomization. To satisfy the treatment compliance, a subject need to complete at least 5 treatments.

|             |                |
|-------------|----------------|
| Trial Code: | HOT-LOCO       |
| Version No: | v.4            |
| Date:       | 2022-01-03     |
| EudraCT No: | 2021-000764-30 |

## 7.3 Packaging, labeling, and handling of investigational products(s)

Treatment: 100% oxygen for medical use, cryogenic gas from hospital supply system. There will be no study-specific packaging or labeling.

Placebo: Compressed air from hospital supply system. There will be no study-specific packaging or labeling.

Treatments will be recorded in the eCRF, the code will be unblinded for staff administering the treatments but assessor-blinded. After the subjects end of study, the code will be broken and recorded in the medical records.

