### **HBO2 SOP and assessment**

A standard operation procedure (SOP) will be attached in the Trial Master File (TMF) but in general terms:

Subjects will be introduced to the hyperbaric unit; if required the subject may visit the unit before the first treatment. Treatment will be conducted in the multiplace (HAUX-STARMED-QUADRO 3500-2400) or monoplace chamber (SECHRIST 3300) depending on availability and number of subjects, at the discretion of the responsible physician. Subjects will be treated for 90 minutes; the treatment protocol is as follows - HBO2 240 kPa with 10 min compression time and 10 minutes decompression time, and two air breaks, while placebo entails - 134kPa air, with 5 min compression time, and 5 min decompression to 120 kPa, and two air breaks will be reported to the subjects. Pressure gauges that can be seen by subjects will be covered. The frequency of the treatments and timing will depend on available resources at the discretion of the responsible physician but should be 2–5 treatments per week for 2–4 weeks. No treatment must be given more than 6 weeks after randomization.

Date and time for treatment will be recorded. Any planned treatment that could not be delivered and reason for the cancellation will be recorded. The treatment will be recorded on a separate CRF accessible only to staff designated to the treatment but blinded for the investigators performing assessments. Treatment type will be recorded in the eCRF and medical records once the code is broken or at the end of trial.

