## 5.3 End of Trial

The end of trial is defined as the last subject's final follow-up at visit 5 (week 52).

Premature termination of this clinical trial may occur because of a regulatory authority decision or at the discretion of the sponsor/the steering committee.

The sponsor/steering committee reserves the right to discontinue the trial at any time point in the following cases:

- Unexpected high proportion of AEs that are possibly or probably related to the trial drug.
- Trial protocol is difficult to cope with.
- Recruitment of eligible subjects is too low.

The end of the trial will be reported to the regulatory authority within 90 days, or 15 days if the trial is terminated prematurely. The Investigators will inform participants and ensure that the appropriate follow up is arranged for all involved.

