## 6.4 Withdrawal Criteria

**Subject participation:** A subject will be considered to have completed the trial when he or she completes the assessment at 52 weeks (visit 5). Subjects should be encouraged to continue the trial but have the right to withdraw their consent or part of their consent regarding the trial participation e.g. to discontinue a study-specific blood test, but still participate in follow-up visits with questionnaires or not participate in further trial visits. The subject has no obligation to explain why he/she does not want to continue. The investigator also has the right to stop the subjects treatment in the event of AEs, protocol deviations, administrative reasons or any other reasons. It is understood by all concerned that an excessive rate of discontinues can render the trial uninterpretable. Therefore, unnecessary discontinuation should be avoided.

Irrespective of the reason for not continuing with the treatments and whenever possible, the patient should be examined. Relevant laboratory test samples should be obtained and all relevant assessments should be completed if applicable. All AEs should be followed up until they have returned to baseline status or stabilised.

A termination visit (End of trial) in the electronic case report form (eCRF) should be completed for every randomised subject whether the subject completed the trial or not. The reason for any early discontinuation should be indicated on this form.

Subjects may be discontinued from the trial at the discretion of the Investigator. Specific reasons for discontinuing a subject from further assessments are:

**AEs:** Clinical or laboratory events that in the judgment of the investigator, DSMB or the Sponsor and in the best interest of the subject constitute grounds for discontinuation. This includes serious and non-serious AEs regardless of relation to trial drug.

**Withdrawal of Consent:** If a subject withdraws consent for disclosure of future information at the discontinuation of the trial or after completion of the trial, no further evaluations should be performed and no additional data should be collected. The Sponsor may retain and continue to use data collected before subject withdrew his/her consent. The Withdrawal of Consent reason is only applicable if the subject denies any further contact with site and no further data collection.

|             |                |
|-------------|----------------|
| Trial Code: | HOT-LOCO       |

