## 7.7 Code breaking

The code is kept in the TMF in sealed envelopes, only accessed by staff designated to the hyperbaric unit if needed for safety reasons. If an AE or an SAE is reported, the PI should immediately assess the causal relationship and if an AR or SUSAR is suspected the code may be broken. Treatment type will be recorded in the medical records once the code is broken or at the end of trial.

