# 9. Statistics

## 9.1 Statistical Analysis Plan

The principal features of the statistical analysis of the data are described in this section. A more technical and detailed elaboration of the principal features will be written in a separate Statistical Analysis Plan (SAP). The SAP will be finalised prior to Data Base Lock (DBL) and will include a more technical and detailed description of the statistical analyses described in this section. This section is a summary of the planned statistical analyses of the most important endpoints including primary and key secondary endpoints.

Trial Code: HOT-LOCO  
Version No: v.4  
Date: 2022-01-03  
EudraCT No: 2021-000764-30

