## 9.1.1 Analysis population

### 9.1.1.1 Definition of Trial Populations

- 9.1.1.1.1 The Full Analysis Set (FAS) Population; All randomized subjects who were exposed at least once to the study intervention will be included in the FAS population.
- 9.1.1.1.2 Per-Protocol (PP) Population; All randomized subjects with no major protocol violations will be included in the PP population. The final decisions regarding the PP population will be taken at the Clean File meeting before the database lock.
- 9.1.1.1.3 Safety Population; All randomized subjects that have received at least one treatment will be included in the safety population.

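### Section 7.3 ends blinding at the subject's end of study, while 5.2.1 and 7.7 point to the end of trial; read per subject, 7.3 would open allocations before the last week-13 outcome and before the SAP and PP set must be final

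*Protocol*

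**What the plan says.** Three places in the protocol govern when allocation is disclosed.

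- **Section 7.3:** "After the subjects end of study, the code will be broken and recorded in the medical records". The possessive has no apostrophe, but the natural reading is one subject at a time.
- **Section 5.2.1 (HBO2 SOP and assessment):** "Treatment type will be recorded in the eCRF and medical records once the code is broken or at the end of trial".
- **Section 7.7 (Code breaking):** "Treatment type will be recorded in the medical records once the code is broken or at the end of trial".

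Two definitions bear on these. Section 5.3 (End of Trial) takes the trial as a whole: "The end of trial is defined as the last subject's final follow-up at visit 5 (week 52". Section 6.4 treats a single subject as complete at that subject's own week-52 assessment, and it also attaches the term to individuals: "A termination visit (End of trial) in the electronic case report form (eCRF) should be completed for every randomised subject".

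On decisions that should be made blind, section 9.1 requires the SAP only before database lock. Section 9.1.1.1 adds: "The final decisions regarding the PP population will be taken at the Clean File meeting before the database lock". No lock date is given. The meeting schedule in section 10.6 places an efficacy analysis when all 80 subjects have completed visit 3, which is before the end of trial.

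**The concern.** If site staff follow 7.3 literally, allocations of early subjects enter medical records while later subjects have not yet reached the primary endpoint at week 13.

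Sections 5.2.1 and 7.7 do not prevent this. Each also allows recording once the code is broken, and 7.3 breaks it. Under 5.2.1 the treatment type then goes into the eCRF as well.

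The choices exposed are those the protocol leaves open until lock: the multiplicity details (9.2.2.2 defers them to the SAP), the imputation method (9.2.8 does not name one) and PP membership. With outcome and arm both visible for a sizeable fraction of subjects, these could be settled with knowledge of how they affect the result.

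Subjects who stop early are a separate case. Their end of study could fall before week 13, while section 8.4 keeps following suspected treatment-related events at planned visits after withdrawal. Follow-up, and the classification of why they left (6.4), could then be done unblinded.

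**Working it through.** The protocol gives no figure on this point, so there is none to reproduce.

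**Inputs**
- 80 subjects (Synopsis; 9.2.1).
- Trial period Q3 2021 to Q4 2023 (Synopsis). Depending on the day within each quarter, its length T is 130.4 weeks (1 July 2021 to 31 December 2023), 117.4 weeks (15 August 2021 to 15 November 2023) or 104.4 weeks (30 September 2021 to 1 October 2023).
- Primary endpoint at week 13 (4.3). A subject's completion is at week 52 (6.4), with a window of 4 weeks either side (5.2, Visit 5).
- Assumptions: uniform accrual, no drop-out, and a trial period that runs from first randomisation to last visit 5. The protocol gives no accrual rate and no last-randomisation date.

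**Formulas, per-subject reading**
- Accrual time: R = T − 52.
- Subjects randomised after the first code opens: 80 × (R − 52) / R.
- Codes open before the last week-13 visit: 80 × (R + 13 − 52) / R.

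| T (weeks) | R (weeks) | Randomised after first code opens | Codes open before last week-13 visit |
|---|---|---|---|
| 130.4 | 78.4 | 80 × 26.4 / 78.4 ≈ 27 | 80 × 39.4 / 78.4 ≈ 40 |
| 117.4 | 65.4 | 80 × 13.4 / 65.4 ≈ 16 | 80 × 26.4 / 65.4 ≈ 32 |
| 104.4 | 52.4 | 80 × 0.4 / 52.4 ≈ 1 | 80 × 13.4 / 52.4 ≈ 20 |

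**Visit-5 window.** With the shortest period and every visit 5 at week 56, R = 48.4 and 80 × (48.4 + 13 − 56) / 48.4 ≈ 9 codes are open before the last week-13 visit. With the longest period and every visit 5 at week 48, R = 82.4 and 80 × (82.4 + 13 − 48) / 82.4 ≈ 46 are open. The gap between first code break and last randomisation runs from −7.6 weeks (no overlap) to 34.4 weeks.

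**Trial-level reading.** If routine disclosure waits for the end of trial in section 5.3, 0 of 80 codes are open before the last week-13 visit.

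**Order of decisions.** A lock holding every week-13 outcome cannot precede the last week-13 visit. On the per-subject reading, some codes are therefore open before the latest date at which the SAP and PP set may be settled.

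**Alternative trigger: release at the week-13 lock.** At the last week-13 visit, anyone randomised in the preceding 52 − 13 = 39 weeks has not reached week 52. That is 80 × 39 / R, or about 40, 48 and 60 of 80 for R = 78.4, 65.4 and 52.4.

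**The case against.** The strongest reply is that 7.3 is only loosely worded. Section 7.7 is the one devoted to code breaking, and with 5.2.1 and 5.3 it supports a trial-level reading under which nothing is opened early. That reading is possible, so what is certain is an inconsistent trigger, not an intended plan to unblind subjects one at a time.

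A reader might infer more than the protocol supports:

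- **That recruitment will certainly overlap with open codes.** No accrual dates are given, and at the short end there is no overlap. The long end needs a first randomisation around 1 July 2021, one day after the version dated 2021-06-30 for submission to the medicines agency, whose approval section 11.2 requires first. That end is implausible.
- **That staff could predict later assignments.** Codes opened at week 52 come from blocks started about a year before. Block size is not given. Suppose six equal strata (two genders by the three severity bands in 9.2.2.3, an assumption) and 65 weeks of accrual. A stratum then gains a subject about every 5 weeks, so a block of 4 to 6 fills in some 15 to 25 weeks. Only a very sparse stratum would still have its block open.
- **That the primary outcome is biased, or the trial is no longer double-blind.** RAND-36 is self-completed and sent digitally. A completer's own week-13 score is collected about 39 weeks before that subject's code opens, and other continuing subjects remain blinded.

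PP is also only a sensitivity analysis (9.2.2), section 7.4 gives it a treatment-count rule, and the SAP may be signed well before its deadline. These points narrow the routes of bias. They do not reconcile the triggers, and none of them makes blind sign-off a requirement.

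**Conclusion.** The point holds as an inconsistency with a real consequence. Sections 7.3, 5.2.1 and 7.7 do not share one trigger, the term end of trial is used both for the trial and for individuals, and no passage keeps routine code breaking behind a final SAP and PP set. Followed as naturally read, 7.3 would open roughly 20 to 40 of 80 allocations before the last week-13 outcome, or about 9 to 46 across the visit-5 windows. Those figures rest on uniform accrual and on the stated trial period being met. Some early disclosure relative to the last primary outcome appears in every scenario computed. Overlap with randomisation appears in most but not all.

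The exposure lies mainly in SAP, PP and discontinuation decisions. Block prediction and bias in the primary outcome are minor, and the protocol does not support a claim that the double-blind design fails. The change is worth making because it is specific and cheap.

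**What to change.** Delete the sentence in 7.3 and use one rule in 5.2.1, 7.3 and 7.7. Apart from individual safety code breaks, no allocation is entered in medical records or in an eCRF visible to blinded staff, or told to subjects, before both the end of trial as defined in section 5.3 (last subject's week 52) and database lock. This also covers subjects who stop early. Use a different term for the per-subject termination visit in 6.4.

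State that the SAP and PP set are signed off before any unblinded analysis by or for the trial team; the DSMB's interim reviews run under their own protocol (9.2.7). If the week-13 efficacy analysis is run before the end of trial, site staff and subjects stay blinded through week 52.

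Release at the week-13 lock would not be a safe shortcut. By the count above, about 40 to 60 of 80 subjects could learn their arm before the self-reported week-52 RAND-36 and EQ-5D, which are efficacy endpoints in 4.4.2.

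The cost is protocol wording, and early subjects wait longer to learn their allocation.

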## 7.4 Drug accountability and treatment compliance

HBO2 is delivered inside a hyperbaric chamber by inhaling 100% oxygen through a tight facemask (in selected cases a hood) attended by medical staff, or inside a monoplace chamber filled with oxygen. If the mask/hood is tight the inspired oxygen pressure is 233.7–240kPa (range depending on 100% saturated - dry gas) at 240 kPa pressure, hence there is no uncertainty about compliance. During compression/decompression patients may need to remove the mask in order to equalize the middle ears and the time might differ slightly between monoplace and multiplace chambers. The difference in dose during this period is negligible. The date and time of treatment will be recorded in the eCRF. Compliance will be measured as the number and fraction of treatments planned vs given. Subjects that have been given at least 5 treatments will be analysed in the PP population. Any discrepancies from the protocol should be recorded in the eCRF.

## 7.5 Randomization

Subjects will be enrolled consecutively, as they are found to be eligible for inclusion in the trial, and randomized but after the treatment has been scheduled. Treatment should start within two weeks of randomization.

If a subject discontinues their trial participation, their subject code will not be reused, and the subject will not be allowed to re-enter the trial again. There will be no replacement for these subjects.

Eligible subjects will be randomized in a 1:1 allocation, stratified by disease severity in relation to RAND 36 and gender in blocks (blinded to all study personnel) to either HBO2 or Placebo. There will be a computer generated randomization.

|             |                |
|-------------|----------------|
| Trial Code: | HOT-LOCO       |
| Version No: | v.4            |
| Date:       | 2022-01-03     |
| EudraCT No: | 2021-000764-30 |

## 7.6 Blinding

This is a double-blind placebo-controlled trial where subjects and all study personnel that participate in the assessment of symptoms and objective findings will be blinded to the treatment. The placebo protocol is well established and even experienced divers cannot differ between “sham treatment” and HBO2 (Lansdorp and van Hulst, 2018). It is not unlikely that some subjects may have problems equalizing the ears even during placebo. Pressure gauges that can be seen by subjects will be covered and all staff will be informed not to discuss the treatment settings when subjects can hear and they will report two air brakes in the same manner as a normal treatment. To validate the blinding process all subjects will be asked at the end of the treatment if they believe they received placebo or HBO2 and AE directly attributed to equalization problems will be compared.

## 7.7 Code breaking

The code is kept in the TMF in sealed envelopes, only accessed by staff designated to the hyperbaric unit if needed for safety reasons. If an AE or an SAE is reported, the PI should immediately assess the causal relationship and if an AR or SUSAR is suspected the code may be broken. Treatment type will be recorded in the medical records once the code is broken or at the end of trial.

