## List of used acronyms and abbreviations

| Abbreviation        | Term/Explanation                                                                                                            |
|---------------------|-----------------------------------------------------------------------------------------------------------------------------|
| 6 min walk test     | 6 minutes walk test (assessment of physical endurance)                                                                      |
| 30/60 s chair stand | 30/60 seconds chair stand (assessment of functional muscle strength)                                                        |
| AE                  | Adverse Event = any untoward medical occurrence                                                                             |
| ANCOVA              | Analysis of Covariance                                                                                                      |
| AR                  | Adverse Reaction = adverse event, that is each unfavorable and unexpected reaction to a trial treatment, regardless of dose |
| ASA Class           | ASA Physical Status Classification System                                                                                   |
| BP                  | Blood Pressure                                                                                                              |
| CAT                 | COPD Assessment Test                                                                                                        |
| COPD                | Chronic Obstructive Pulmonary Disease                                                                                       |
| COVID-19            | Corona Virus Disease 2019                                                                                                   |
| CRA                 | Clinical Research Associate                                                                                                 |
| CRO                 | Contract Research Organization                                                                                              |
| CT                  | Computerized Tomography                                                                                                     |
| CXR                 | Chest X-Ray                                                                                                                 |

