### **Socio-demography**

Demographic data such as gender, age, level of education, rate of employment/studies, level/rate of exercise, country of origin, body weight, height, and smoking habits/ nicotine use will be collected at Visit 1. Records and medical history will be reviewed for update/change in parameters at each visit.

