#### 8.1.2 Adverse Reaction (AR)

In the new use of a medicinal product all noxious and unintended reactions to the medicinal product related to any dose should be considered an adverse reaction (AR). The phrase 'reaction to a medicinal product' means that the causal relationship between the medical product and an adverse event is at least a reasonable possibility, that is the relationship cannot be ruled out.

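### Section 7.7 lets any suspected adverse reaction open the code and puts the arm in records used at later visits, so assessors may be unblinded before week 13

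*Protocol*

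**What the plan says.** **Who may open the code, and when.** Section 7.7 keeps the code in sealed envelopes, "only accessed by staff designated to the hyperbaric unit if needed for safety reasons". The next sentence says that on report of an AE or SAE "the PI should immediately assess the causal relationship and if an AR or SUSAR is suspected the code may be broken".

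**What counts as an AR.** Section 8.1.2 covers unintended harmful reactions at any dose, without a severity limit. Its threshold reads: "the causal relationship between the medical product and an adverse event is at least a reasonable possibility, that is the relationship cannot be ruled out". The abbreviation list instead describes an AR as "each unfavorable and unexpected reaction to a trial treatment, regardless of dose".

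**What happens after a break.** Section 7.7: "Treatment type will be recorded in the medical records once the code is broken or at the end of trial". The hyperbaric treatment paragraph of 5.2.1 says the same and adds the eCRF. That paragraph also sets up a separate treatment CRF, open only to treatment staff and closed to the investigators who perform assessments.

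**Who reads those records.** The trial schedule lists a review of medical records at visits 2, 3, 4 and 5; visit 3 is the week-13 primary time point. The socio-demography paragraph adds, for its own items, that "Records and medical history will be reviewed for update/change in parameters at each visit". Under 8.3 the investigator judges causality, severity and seriousness directly in the eCRF.

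**What blinding is promised.** Section 7.6 says that subjects, and all personnel who assess symptoms and objective findings, are blinded. Section 7.3 says that "the code will be unblinded for staff administering the treatments but assessor-blinded".

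**The concern.** A code break for a non-serious reaction would fall in the treatment period, because 8.3 records non-serious events only then. That is before the week-13 assessments. Staff who give the sessions already know the allocation (7.3), so opening an envelope informs mainly people who are meant not to know it, and the entry in the records and eCRF can inform more of them.

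The outcomes that depend on staff judgement are then exposed:

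- The 6-minute walk and chair-stand tests are run by staff, and in the chair stand the subject is encouraged aloud.
- The investigator rates the causality of adverse events.
- The investigator decides whether a symptom belongs to Long COVID, in which case it is not recorded as an adverse event (8.3).
- Treatment failure is judged by the investigator (6.4).

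If reactions that prompt a break differ in frequency between 240 kPa oxygen and 134 kPa air, the loss of blinding would differ by arm as well.

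**Working it through.** **Step 1: the passages side by side.**

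| Question | One place | Another place |
|---|---|---|
| Ground for a break | 7.7, envelope sentence: safety need | 7.7, next sentence: any suspected AR or SUSAR, with no stated need to know the arm |
| Is an AR unexpected by definition? | Abbreviation list: yes | 8.1.2: no such limit |
| Where is treatment type kept? | 5.2.1: restricted treatment CRF | 7.7 and 5.2.1: medical records, and eCRF, once the code is broken |
| Are assessors blinded? | 7.6: yes | Schedule and 8.3: records reviewed and eCRF used at visits, with no shielding stated |

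Naming AR beside SUSAR means that the event need not be serious. Sections 8.3.2 and 8.3.3 give expectedness and SUSAR assessment to the sponsor, whereas 7.7 acts on the principal investigator's suspicion.

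**Step 2: how many subjects, at the protocol's own rate.** Section 3.2 gives 40 complications per 10,000 treatments. The itemised rates are 20 + 8 + 5 + 2 + 2 + 1 = 38, with chest pain listed without a number, so the total is consistent. Other inputs are 80 subjects at 1:1, hence 40 per arm; at most 10 treatments (5.1); and at least 5 for compliance (7.2). Treatments are assumed independent.

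Per subject: p = 1 − (1 − r)^k. Expected subjects: 40p. Chance of at least one in the arm: 1 − (1 − p)^40.

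| Event | r | k | p | 40p | At least one in arm |
|---|---|---|---|---|---|
| Any complication | 0.0040 | 10 | 0.0393 | 1.57 | 0.80 |
| Any complication | 0.0040 | 5 | 0.0198 | 0.79 | 0.55 |
| Ear pain | 0.0020 | 10 | 0.0198 | 0.79 | 0.55 |

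By simple count, 400 sessions × 0.0040 = 1.6 complications. Breaks in the HBO2 arm would thus lie between 0 and about 1.6 subjects, depending on how often the discretion is used.

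**Step 3: range under assumed rates.** The document gives no sham rate, no suspected-AR rate and no code-break rate. The percentages below are assumptions. The cells show subjects unblinded, HBO2 versus sham, out of 40 each.

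| Suspected AR, HBO2 vs sham | 10% lead to a break | 50% | 100% |
|---|---|---|---|
| 4% vs 2% | 0.16 vs 0.08 | 0.8 vs 0.4 | 1.6 vs 0.8 |
| 10% vs 5% | 0.4 vs 0.2 | 2 vs 1 | 4 vs 2 |
| 30% vs 10% | 1.2 vs 0.4 | 6 vs 2 | 12 vs 4 |

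**Step 4: bound on the primary endpoint, if subjects also learned their arm.** If m HBO2 subjects each moved b points, the arm mean moves m × b / 40. With b assumed at 5 to 10 points: m = 2 gives 0.25 to 0.5; m = 4 gives 0.5 to 1.0; m = 12 gives 1.5 to 3.0. The target difference in 9.2.1 is 10 points.

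**The case against.** The break is permissive, and the preceding sentence limits access to hyperbaric-unit staff with a safety reason. Read together, the two sentences can mean that a suspected AR permits a break only when safety requires it. Since treating staff already know the arm, there would seldom be a reason to open an envelope for mild ear pain. This stands as a reason to expect few breaks. It does not settle the text, because the second sentence states its ground without that condition. Section 3.5 also makes the principal investigator head of the unit, so the access limit does not clearly exclude that role.

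The protocol does not name who reviews the records at each visit, nor say that the principal investigator assesses outcomes. That also stands: exposure of assessors is possible, not certain. The main secondary endpoints are declared exploratory (9.2.2.2) and adverse events are compared descriptively (9.2.6.1), which lowers the stakes further.

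A reader might infer three stronger points, and the document supports none of them:

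- **Blinding will be lost more often on HBO2.** This is plausible, but no sham or code-break rate is given, and 7.6 expects some ear problems on placebo too.
- **Mild, expected reactions plainly qualify.** That follows from 8.1.2, but the abbreviation list restricts ARs to unexpected ones. The conflict is itself something to correct.
- **The primary endpoint is biased.** RAND-36 is self-reported and sent digitally, and nothing says that subjects are told their arm after a break.

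**Conclusion.** The point holds as a defect of wording. Section 7.7 fixes a ground for breaking the code that is wider than its own safety limit, and 7.7 and 5.2.1 then place the arm where personnel promised blinding by 7.6 may read it before week 13.

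The effect is of unknown size and probably small. About 1.6 of 40 HBO2 subjects would have a complication at the protocol's rate, assuming 10 independent treatments each; the number of breaks would be no higher at that rate. Larger figures need a higher suspected-AR rate, which the wide definition in 8.1.2 makes possible but the document does not give. Any difference between arms is a possibility only. The threat is chiefly to the walk and chair-stand tests, adverse-event causality and Long COVID attribution. It is worth correcting because the correction is cheap, not because the primary result is in doubt.

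**What to change.** 1. **Reconcile the two sentences of 7.7.** Suspicion of a non-serious AR should not by itself be a ground. A break should require that knowing the allocation is needed for the subject's safety, or for SUSAR reporting by persons outside outcome assessment. When safety requires it remains a judgement for those responsible for the subject; safety-driven unblinding stays intact.
2. **Amend 7.7 and the hyperbaric treatment paragraph of 5.2.1 together.** After a break, treatment type stays in the restricted treatment CRF and is withheld from outcome assessors until the trial code is opened, unless the subject's care requires otherwise. Changing 7.7 alone would leave the 5.2.1 instruction contradicting it.
3. **Align the AR definitions** in 8.1.2 and the abbreviation list on expectedness.
4. **Log every break** by arm and date, in restricted storage, so that its extent can be reported.

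Cost: protocol wording and a short instruction to the hyperbaric unit. The causality of non-serious ARs would be judged without knowledge of the arm. The restricted CRF already exists, and neither the sample size nor the analysis changes.
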